### 5.8 Standardized questionnaires

Two standardized questionnaires will be administered to patients enrolled in the GLUMIT-DG study. Questionnaires will be administered at baseline (prior to enrollment) and during follow-up at specified intervals (see Appendix 10.2 for the data collection schedule). The purpose of the questionnaires is to obtain important information regarding gastroparesis symptoms and health-related quality of life.

#### **Patient Assessment of Upper Gastrointestinal Disorders - Symptom Severity Index (PAGI-SYM).**

A validated 20 question questionnaire that measures symptoms of gastroparesis, dyspepsia, and gastroesophageal reflux disease on a 0 to 5 scale for each symptom^18.

**Patient Assessment of Upper Gastrointestinal Disorders - Quality of Life (PAGI-QOL).** A validated 30 question questionnaire that measures quality of life in upper gastrointestinal disorders.

### 5.9 Specimen repository

Ten milliliters of blood will be collected for plasma separation and banking at screening and at follow-up 12 and 24 week visits. Plasma will be separated and stored for use as approved by the Steering Committee of the GpCRC (see Appendix 11.3 for whole blood draw schedule). The blood will be drawn in the morning during the study visit while the patient is still fasting. The blood will be separated into plasma and will be divided into 0.5 mL aliquots. Plasma aliquots will be kept in a freezer at -70 degrees C and will be sent to the NIDDK Biosample Repository for banking. The plasma will be analyzed for inflammatory, immune markers, or plasma proteins for the effects controlling blood glucose has on disease biomarkers.

---

## 6. Safety Issues

---

Safety issues can be divided into (a) safety concerns related to insulin pump therapy, (b) safety issues related to RT-CGM, (c) safety concerns related to management of hypoglycemic and hyperglycemic episodes, (d) safety concerns related to study procedures, and (e) concerns related to patient privacy. The following paragraphs discuss the important potential adverse events and the proposed safeguards to minimize the risks involved by participating in the GLUMIT-DG study.

### 6.1 Safety concerns related to insulin pump therapy and CGM

Patients in this study will use the glucose meter as well as MiniLink REAL-Time Transmitter and insulin pump. Because the insulin infusion set and the REAL-time sensor are inserted subcutaneously, there is a risk for the patient to develop an infection. However, with proper technique and good care, the infection risk is small. If patients notice any discoloration of the skin, or signs of inflammation (redness, swelling, pain); they will be required to contact the study investigator immediately. Patients may need treatment with antibiotics, if indicated. The needles may also cause hematomas (the needles may pierce small vessels and blood may leak). Hematomas return to normal unless the areas become infected. Very rarely, some people are allergic to the glue or the material used to secure the insulin infusion sets and sensors to the skin; there may also be itching, redness and swelling. If this reaction occurs, medication administration may be necessary.

### 6.2 Safety concerns related to incidence and management of hypoglycemic episodes

Diabetic patients with gastroparesis run the risk of developing hypoglycemic or hyperglycemic episodes. In the event that a hypoglycemic or hyperglycemic episode should occur, appropriate treatment measures will be taken to resolve the event. A description of the treatment for hypoglycemic and hyperglycemic events during participation in the GLUMIT-DG study is as follows:

#### Mild hypoglycemic episodes

For a **hypoglycemic event** to be considered mild; the capillary glucose will be 50 - 70 mg/dL as confirmed by a finger stick glucose meter reading (SMBG); and the patient is fully capable of self treatment without the need of third party assistance. Mild hypoglycemia may be symptomatic or asymptomatic. The following treatment protocol for mild hypoglycemic episodes will be followed:

1. If the SMBG value is 50 - 70 mg/dL, it should be treated by ingestion of 15-20 grams of carbohydrates (e.g., 4-5 glucose tablets, 5-6 Lifesavers, 4-6 oz. of a regular [non diet] soft drink, or 8 oz. low fat milk, or 4 teaspoons of sugar dissolved in a liquid or juice). If the subject is in the hospital, the SMBG reading will be confirmed by a laboratory glucose measurement, but treatment will be initiated based on the Ultra reading.
2. Blood glucose should be self-tested 15-20 minutes after ingestion of carbohydrates and therapy will be repeated as above, as needed. Cycle should be repeated until glucose level is 80 mg/dL or above.
3. Once episode is resolved, if no meal is scheduled the next 2 hours, a mixed nutrient snack, including a carbohydrate, protein, and fat will be ingested right after the initial therapy and after resolution of episode to prevent another episode.

#### Moderate hypoglycemic episode

For a **hypoglycemic event** to be considered moderate, the capillary glucose will be below 50 mg/dL using a finger stick glucose meter reading (SMBG), and the patient is fully capable of self-treatment, without

the need of third party assistance. The following protocol for treatment of **moderate hypoglycemia** will be followed:

1. If blood glucose level is less than 50 mg/dL, the patient should ingest 30 grams of carbohydrates (e.g., 6-8 glucose tablets). If the subject is in the hospital, the Ultra glucose reading will be confirmed by a laboratory glucose measurement, but treatment will be initiated based on the SMBG reading.
2. The capillary blood glucose will be tested 15-20 minutes after ingestion of carbohydrate and therapy will be repeated as above, as needed, and repeated until glucose level is 80 mg/dL or above.
3. Once the episode is resolved, if a meal is not scheduled within the next 2 hours, a mixed nutrient snack, including carbohydrate, protein, and fat should be ingested right after resolution of episode to prevent another episode.

### **Severe hypoglycemic episodes**

If the capillary glucose level is below 50 mg/dL by an finger stick glucose meter reading (SMBG), and the patient is incapable of self-treatment, hence in need of assistance from a third party (friend, relative, paramedic, etc), the following treatment protocol will be followed:

For patients that are conscious and cooperative and NOT in the Hospital, Clinic or ER:

1. Turn patient on side and administer 1 mg of glucagon (intramuscular, subcutaneous, or intravenous) using the provided kit.
2. Check SMBG value in 10 minutes.
3. If consciousness and cooperation are fully restored and finger stick glucose value is above 80 mg/dL, provide with 20 grams of sugar (e.g., 4-5 glucose tablets, 5-6 Lifesavers, 4-6 oz. of a regular [non diet] soft drink, 8 oz. low fat milk, 4 teaspoons of sugar dissolved in a liquid or juice) and check glucose level again in 20 minutes.
4. If the SMBG value is partially restored >60-80 mg/dL but patient remains conscious and fully cooperative, provide patient with another 20 grams of carbohydrate and repeat cycle until finger stick glucose value is >80 mg/dL and stable.
5. If SMBG value is NOT above 60 mg/dL at the 10 minute check, call 911. If patient is still cooperative, offer 20 grams of carbohydrate; repeat cycle until paramedics arrive.

For patients that are unconscious or neurologically impaired and NOT in the Hospital, Clinic or ER:

1. Turn patient on side and administer 1 mg of glucagon (intramuscular, subcutaneous, or intravenous) using the provided kit.
2. Call paramedics or 911 (if haven't already done so).
3. Check finger stick glucose value in 10 minutes.
4. If consciousness and cooperation are fully restored and finger stick glucose value is above 80 mg/dL and paramedics have NOT arrived, provide patient with 20 grams of sugar (e.g., 4-5 glucose tablets, 5-6 Lifesavers, 4-6 oz. of a regular [non diet] soft drink, or 8 oz. low fat milk, 4 teaspoons of sugar dissolved in a liquid or juice) and check glucose level again in 10 minutes, and provide with a mixed nutrient drink. Check finger stick glucose value every 10 minutes until paramedics arrive.

Whenever possible, all hypoglycemic glucose values will be confirmed by a laboratory glucose measurement, if the subject is in a setting where a laboratory glucose measurement can be obtained.

For those patients with hypoglycemia IN a hospital setting, established protocols of the hospital will be followed including but not confined to administration of dextrose and glucagon as per the clinical judgment of the attending physician.

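### The rescue list for conscious, cooperative patients with severe hypoglycemia contradicts its own heading and gives no step for two of the six states possible at the 10-minute check

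*Protocol*

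**What the plan says.** Protocol section 6.2, under Severe hypoglycemic episodes, applies when capillary glucose is below 50 mg/dL "and the patient is incapable of self-treatment, hence in need of assistance from a third party". The third party may be a friend, a relative or a paramedic. Two lists then cover patients outside hospital, clinic and emergency room.

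**First list**, headed "For patients that are conscious and cooperative and NOT in the Hospital, Clinic or ER":

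- Step 1: glucagon from the kit provided.
- Step 2: "Check SMBG value in 10 minutes".
- Step 3: "If consciousness and cooperation are fully restored and finger stick glucose value is above 80 mg/dL, provide with 20 grams of sugar", with another check in 20 minutes.
- Step 4: "If the SMBG value is partially restored >60-80 mg/dL but patient remains conscious and fully cooperative", give another 20 grams of carbohydrate and repeat the cycle.
- Step 5: "If SMBG value is NOT above 60 mg/dL at the 10 minute check, call 911", and offer carbohydrate if the patient is still cooperative.

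**Second list**, headed "For patients that are unconscious or neurologically impaired and NOT in the Hospital, Clinic or ER":

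- Step 1: the same glucagon step.
- Step 2: an emergency call, required of everyone unless it has already been made.
- Step 3: a glucose check at 10 minutes.
- Step 4: what to give if consciousness and cooperation are fully restored, glucose is above 80 mg/dL and paramedics have not arrived. It ends with glucose checks every 10 minutes until they do.

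**The concern.** The heading of the first list and its step 3 describe different patients. The heading admits people who are conscious and cooperative. Step 3 speaks of consciousness and cooperation coming back, in wording shared with step 4 of the list for unconscious patients. Once step 3 allows that such a patient may not be recovered at the check, the reader needs to know what happens to one who is not, and the first list does not say. Its emergency call depends on the glucose value alone.

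At stake is the clarity of an emergency instruction for use outside hospital, where the person helping may have no clinical training. For patients in hospital, section 6.2 can fall back on hospital protocols and the attending physician's judgment. The two out-of-hospital lists have no such fallback.

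**Working it through.** No figure in the plan has to be reproduced. The check sets the steps of the first list against its heading, and then against every state possible at the 10-minute check.

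**Heading against steps (first list)**

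- Step 3 requires that consciousness and cooperation be restored. The heading says they were present at entry. Steps 4 and 5 use wording that fits the heading: the patient remains conscious, or is still cooperative. Only step 3 is out of line.
- Step 4 gives 'another' 20 grams at >60-80 mg/dL. Before the first check the list gives glucagon only. Carbohydrate first appears in step 3, for values above 80 mg/dL. A patient who is at >60-80 mg/dL at the first check therefore goes straight to step 4 and has had no earlier 20 grams under this list. The word fits only a patient who passed through step 3 and later fell back.

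**States at the 10-minute check**

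Steps 3 to 5 use three glucose bands: not above 60, >60-80 and above 80 mg/dL. These cover every value. Each band is crossed with two mental states (conscious and cooperative, or not), so 3 × 2 = 6 states.

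| Glucose at check (mg/dL) | Conscious and cooperative | Not conscious or not cooperative |
|---|---|---|
| Above 80 | Step 3 | No step in this list |
| >60-80 | Step 4 | No step in this list |
| Not above 60 | Step 5, emergency call | Step 5, emergency call |

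Two of the six states have no step, and in neither is an emergency call triggered by this list. In the top left cell, a patient who never lost consciousness is assumed to satisfy step 3.

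**Second list**

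After the check it has one branch: recovered, above 80 mg/dL, paramedics not arrived. But step 2, "Call paramedics or 911 (if haven't already done so", comes before the check and depends on neither glucose nor recovery, so the call covers all six states.

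**Link between the lists**

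A first-list patient who becomes unconscious or impaired would meet the second heading. No sentence tells the helper to move across. If the helper does, the second list starts again at the glucagon step, and the text does not say whether that step is meant to apply to someone who has just had it.

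**The case against.** The best reply is that the lists are defined by the patient's condition. Whoever loses consciousness or becomes neurologically impaired falls under the second heading, and its step 2 then requires the emergency call. On that reading the two empty cells are mostly filled. This is a fair account of the likely intent, but it is inference. There is no cross-reference, the point of re-entry is unclear, and a patient who is uncooperative without being impaired fits neither list after the check.

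A second reply is that step 3 is loose wording only. Everyone on either list is by definition incapable of self-treatment, so 'fully restored' may mean complete recovery, and a patient who stayed well satisfies it anyway. That stands for the recovered patient, for whom nothing changes. It also concedes that step 3 expects some first-list patients not to be recovered, and those are the ones left without a step.

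Three stronger readings are tempting and not supported:

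- A reader might infer that the second list abandons the gravest cases because it has a single branch after the check. Its unconditional call comes first, and the closing sentence of step 4 can be read as repeat checks for everyone still waiting.
- A reader might infer that the whole first list is conditioned on recovery. Only step 3 of five is.
- A reader might infer harm to the primary safety outcome. An episode is severe because of glucose below 50 mg/dL and the need for third-party help, both settled before any rescue branch is taken.

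**Conclusion.** The point holds for the first list. Step 3 contradicts the heading, 'another' in step 4 does not fit a patient who reaches it at the first check, and two of six states at that check have no step and no emergency call within the list. The missing hand-over to the second list is part of the same defect. The missing branches in the second list are a lesser matter.

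The count rests on reading the steps literally, on the protocol's own glucose bands, and on treating mental state as two categories. If the second list is taken to apply automatically to anyone who deteriorates, the gap shrinks to the missing cross-reference, the unclear re-entry point and the uncooperative but unimpaired patient. The protocol does not show what training or printed material helpers receive, so nothing is assumed about it. Sample size, power and analysis are not affected.

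**What to change.** The study's clinical authors should:

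1. reconcile the heading of the first list with the condition in step 3 and the word 'another' in step 4;
2. reconcile the first list with the second, and state which instruction applies when a first-list patient is not conscious or not cooperative at the 10-minute check, including where in the second list the helper should start if that is the intended route.

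What those instructions should be is for them to decide, and none is proposed here. The cost is rewording within one subsection of section 6.2. No design element, outcome definition or analysis changes.

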### 6.3 Safety concerns related to incidence and management of hyperglycemic episodes

Diabetic patients with gastroparesis run the risk of developing hyperglycemic episodes. In the event that a hyperglycemic episode should occur, appropriate treatment measures will be taken to resolve the event. A description of the treatment for hyperglycemic events during participation in the GLUMIT-DG study is as follows:

#### Mild hyperglycemia episodes

For a **hyperglycemic event** to be considered mild, the capillary glucose will exceed 180 mg/dL up to 300 mg/dL using a finger stick glucose meter reading (SMBG) and there are no blood or urine ketones present and the subject is not nauseated, vomiting or having an altered sensorium. For mild hyperglycemia the following treatment protocol will be followed:

1. The pump settings have been set up to provide extra amounts of insulin as "boluses" based on target for glycemia and estimated insulin sensitivity index (so-called correction factor) as well as estimated residual insulin from previous boluses (proprietary calculation of Medtronic). Patients will be asked to check blood sugar 1 hour following correction to assess effectiveness of correction. In the event the glucose does not drop by 50 mg/dL or more in one hour patients will be asked to use bolus wizard to determine correction dose but not deliver the dose, disconnect from the pump and deliver the calculated dose using a syringe or insulin pen. They will then be asked to change the insulin in the reservoir, the tubing and the infusion set, and continue to monitor blood glucose hourly, until blood glucose is less than 180 mg/dL.

#### Moderate hyperglycemia episodes

For a hyperglycemia event to be considered moderate, the capillary glucose will exceed 300 mg/dL up to 500 mg/dL using a finger stick reading (SMBG). The treatment protocol should be followed:

1. If patients are symptomatic or mildly symptomatic, they will be requested to contact the diabetes educator or diabetologist and decisions will be made via the telephone (self adjustment, a visit to the study doctor, or an emergency department visit) based on individual circumstances.
2. Patients with type 1 diabetes will be required to test themselves for ketones using the ketone-meter strips provided to them. If the ketonemia is equal or greater than 0.6 mM/L, the patient will be requested to change the infusion setting of the pump and additional insulin may be provided with injections to avoid further progression into ketoacidosis. Patients will be asked to check blood sugar with SMBG 1 hour following correction to assess effectiveness of correction. In the event the glucose does not drop by 50 mg/dL or more in one hour patients will be asked to use bolus wizard to determine correction dose but not deliver the dose, disconnect from the pump and deliver the calculated dose using a syringe or insulin pen. They will then be asked to change the insulin in the reservoir, the tubing and the infusion set, and continue to monitor blood glucose hourly, until blood glucose is less than 180 mg/dL and blood ketones are less than 0.6 mM/L.
3. If the glycemia and ketonemia do not improve or worsen or the endocrinologist judges it necessary, the patient will be requested to visit the emergency department.

#### Severe hyperglycemia episodes

For a **hyperglycemic event** to be considered severe the capillary glucose will exceed 500 mg/dL using a finger stick glucose meter reading (SMBG) and/ or patients may have ketones as evidenced by blood

ketone test of 0.6 mmol/L or higher or large urine ketones and/or the presence of nausea, vomiting or altered mental status. The following treatment protocol will be followed:

1. If patient is symptomatic (polyuria, polydipsia) or with concurrent illness, but capable of good communication, a phone contact to diabetologist is mandatory who will make the decision regarding a visit to see the study doctor or emergency department visit.
2. If symptoms are intense or the patient is incapable of good communication, immediate transport to emergency department should precede the phone contact.

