### 7.1 Definitions

**Adverse event:** An adverse event is any untoward medical occurrence that may present itself during a research study which may or may not have a causal relationship with the treatment or study participation. Adverse events include any unanticipated problems involving risks to participants, or breaches of protocol which might entail risk to participants. The term “unanticipated problem” includes both new risks and increased occurrence of anticipated problems.

**Severe hypoglycemic events** occur when a patient’s capillary glucose falls below 50 mg/dL and the patient is incapable of self treatment, hence needing the assistance of a third party (friend, relative, paramedic, etc) for resolution of the hypoglycemia. This type of event will be recorded on study form(s). If a patient has more than two severe hypoglycemic events (i.e., ER visit, relative, etc.) during the study, he/she will be re-evaluated with the diabetologist with an option to be placed back on the previous diabetes medications or insulin regimen. Study staff will follow up with patients to ensure that severe hypoglycemic events were properly managed and make any necessary modifications to their treatment.

**Severe hyperglycemic events** occur when a patient’s capillary glucose is above 500 mg/dL as revealed on an finger stick reading (SMBG, confirmed by a reference glucose value if available) and/or a blood ketone test of 0.6 mmol/L or higher and/or the presence of nausea, vomiting or altered mental status. The patient may be symptomatic (polyuria, polydipsia) or with concurrent illness, but capable of good communication or the patient’s symptoms may be intense, or the patient is incapable of good communication and immediate transport to emergency department may be necessary. These severe hyperglycemic events will be recorded on study case report forms according the procedures for SAEs in Section 7.3.

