**Serious adverse event:** A serious adverse event (SAE) is an adverse event occurring at any time during the study that results in death, life-threatening adverse experience, inpatient hospitalization or prolongation of existing hospitalization, a persistent or significant disability or incapacity, or a congenital anomaly or birth defect. Severe hypoglycemic and severe hyperglycemic events will be considered an SAE. Other events may also be considered an SAE if, based on medical judgment, the event jeopardized the patient to the point of requiring medical or surgical intervention to prevent the occurrence of any of the conditions for an SAE listed above.

**Sentinel events** are defined as the subset of serious adverse events involving severe hypoglycemic (<50 mg/dL) or hyperglycemic (>500 mg/dL) occurrences AND any of the following: loss of consciousness, seizures, hospitalization, emergency room visit, professional intervention, or death.

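### A reading above 500 mg/dL is by itself a severe event and an SAE, yet section 6.3 requires the diabetologist call only if symptoms, illness or poor communication are also present

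*Protocol*

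**What the plan says.** **Definition.** Section 6.3 (Severe hyperglycemia episodes) classes an event as severe when "the capillary glucose will exceed 500 mg/dL using a finger stick glucose meter reading (SMBG) and/ or patients may have ketones", with further alternatives covering gastrointestinal symptoms and altered mental status. Section 7.1 (Definitions) has the same structure: it starts from "capillary glucose is above 500 mg/dL as revealed on an finger stick reading" and links the ketone and symptom criteria by and/or. It then describes presentation permissively: "The patient may be symptomatic (polyuria, polydipsia) or with concurrent illness, but capable of good communication".

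**Status.** Section 7.1 also states: "Severe hypoglycemic and severe hyperglycemic events will be considered an SAE".

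**Severe-tier instructions.** Section 6.3 gives two. Item 1: "If patient is symptomatic (polyuria, polydipsia) or with concurrent illness, but capable of good communication, a phone contact to diabetologist is mandatory". Item 2: "If symptoms are intense or the patient is incapable of good communication, immediate transport to emergency department should precede the phone contact".

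**Lower tiers.** The mild tier applies when "the capillary glucose will exceed 180 mg/dL up to 300 mg/dL", and its correction step continues: "Patients will be asked to check blood sugar 1 hour following correction to assess effectiveness of correction". If glucose has not fallen by at least 50 mg/dL in that hour, the patient doses by syringe or pen and replaces the reservoir insulin, tubing and infusion set. The moderate tier runs from above 300 to 500 mg/dL. It repeats these steps within an item that opens with required ketone testing for type 1 patients, and its item 3 sends the patient to the emergency department if glycemia and ketonemia fail to improve or get worse.

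**The concern.** The rule that defines the event and the rule that prescribes the response have different triggers. The definition needs only a number. The response needs a number plus symptoms, concurrent illness or impaired communication. A patient who meets the first but not the second has, by the protocol's own classification, an SAE for which section 6.3 states no action.

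This matters because participants stop their previous diabetes treatment and rely on pump insulin (section 5.4, Run-in visit 3). The mild and moderate tiers foresee a failed infusion, since they tell the patient to bypass the pump and change the set when a correction does not work. The severe tier does not repeat that safeguard, and the general correction for readings above 180 mg/dL (section 2.4) is delivered through the same pump. Patients apply these instructions at home across seven centers, so the exact wording carries weight.

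**Working it through.** No arithmetic applies and the plan gives no figure to reproduce. The check is to follow a defined patient through the text.

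**Test patient.** First reading 510 mg/dL (an illustrative value above the threshold), no symptoms, no concurrent illness, communicates well, either type of diabetes.

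| Rule | Protocol location | Met? |
|---|---|---|
| Severe event (above 500 mg/dL is enough) | 6.3 Severe; 7.1 | Yes |
| SAE | 7.1 | Yes |
| Mandatory call: symptoms or concurrent illness | 6.3 Severe, item 1 | No |
| Emergency transport, then call: intense symptoms or unable to communicate | 6.3 Severe, item 2 | No |
| Mild-tier correction steps (above 180, up to 300 mg/dL) | 6.3 Mild | No |
| Moderate-tier steps (above 300, up to 500 mg/dL) | 6.3 Moderate | No |

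So section 6.3 states neither a contact nor a treatment step for this patient.

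**Comparison just below the threshold.** A symptom-free type 1 patient at 490 mg/dL falls in the moderate tier. That patient must test ketones, is asked to recheck one hour after correction, and has the syringe-or-pen and set-change steps if glucose has not dropped by 50 mg/dL. No call is required there either, because moderate item 1 is also tied to symptoms. The step from 490 to 510 mg/dL therefore removes the stated self-treatment steps and adds SAE status, with no contact requirement to match.

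**Same gap on the ketone criterion.** Under sections 6.3 and 7.1, blood ketones of 0.6 mmol/L or higher also suffice for a severe event. A symptom-free patient at or below 500 mg/dL who qualifies only through ketones has no mandatory call. For type 1 patients between 300 and 500 mg/dL, moderate item 2 supplies a home procedure, so what is missing for them is the call.

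**Episodes that do not start above 500 mg/dL.** After a failed correction, the mild and moderate steps require hourly glucose checks until the value is below 180 mg/dL, and they do not lapse when 500 mg/dL is crossed. Moderate item 3 asks for an emergency visit if the episode worsens. These episodes are therefore partly covered, and what remains is mainly the episode first detected above 500 mg/dL.

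**Other safeguards that apply at any level.**
- Section 5.4: a high-glucose alarm at 240 mg/dL with a snooze of 1 to 2 hours, so a patient wearing the sensor who stays high is prompted again.
- Sections 3.3, 4.4 and 6.6: meter checks at least four times a day as a competency and adherence standard.
- Section 5.5: training to act on meter results.
- Section 5.6: weekly staff review of glucose data through CareLink.

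None of these requires contact with the diabetologist when the reading occurs.

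**The case against.** The strongest reply is that the patient is not left alone. The alarm sounds again within hours, meter checks recur through the day, and a patient taught the moderate steps would probably use them at 510 mg/dL as well. Item 2 speaks of the phone contact as though it were expected in any severe case, and it reaches patients who cannot communicate whatever their symptoms. An episode climbing through the moderate tier is still being monitored.

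Most of this stands, and it narrows the point. It does not close it: the moderate steps are bounded at 500 mg/dL, the severe tier is introduced with its own treatment protocol, and both items of that protocol carry a condition that the test patient does not meet.

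A reader might infer more than the documents support:
- **That the patient goes up to a week unchecked.** The weekly interval is a staff review. Patient-level prompts come much sooner, so it should not be set against the one-hour self-check.
- **That SAE reporting is late by a definite number of days.** Staff notice could wait until the weekly review, but the protocol states no upload interval. The 72-hour limit in section 7.3 runs from the time the center determines that an SAE has occurred. Any figure for days to report would rest on assumed uploads, and no deadline is shown to be broken.
- **That the SAE is never captured.** Uploads, weekly review and visits would probably bring the reading to notice.

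**Conclusion.** The point holds in a narrow form. For a symptom-free patient who communicates well and whose first reading is above 500 mg/dL, the protocol declares an SAE but states neither a required contact nor a severe-tier step. The ketone-only severe event lacks the mandatory call in the same way. This is a stated safety rule tied to the wrong trigger, rather than detail left for another document.

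Its size cannot be put into numbers, because the protocol gives neither the frequency of readings above 500 mg/dL nor the share without symptoms. The primary outcome is hypoglycemia, so the primary analysis, its power and the 35% limit are untouched.

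The conclusion rests on two readings: that and/or in the definitions is inclusive, which the permissive wording on symptoms in section 7.1 supports, and that the two severe-tier items are the whole of that tier's protocol, since section 6.3 lists nothing else. It is worth correcting because the event is one the protocol itself treats as serious and the correction is cheap.

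**What to change.** In section 6.3, Severe hyperglycemia episodes:

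1. Make phone contact with the diabetologist mandatory for any reading above 500 mg/dL and for blood ketones of 0.6 mmol/L or higher, regardless of symptoms or diabetes type.
2. Keep emergency transport ahead of the call when symptoms are intense or the patient cannot communicate.
3. State that the moderate-tier steps (correction, one-hour recheck, syringe or pen dose, change of reservoir insulin, tubing and set) also apply above 500 mg/dL while contact is being made, with ketone testing for type 1 patients using the strips already supplied.

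The cost is a few sentences of protocol text, some additional phone calls and ketone self-tests, and occasional study-doctor or emergency visits that the diabetologist decides on. No scheduled visit needs to be added, and the analysis does not change.
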